### Statistical analysis

The large amount of heterogeneous data to be recorded and collected for each participant will be analysed using R and visualised using R Shiny apps. Any changes in adherence to physiotherapy prescriptions or recommendations over time or in relation to ACT gaming or feedback, will be quantified. As CF phenotypes and physiotherapy adherence are complex and multifactorial, cluster analysis will define groups of individuals based on measured characteristics to identify subgroups of participants with distinct physical activity and/or ACT adherence profiles.

The Fitbit and ACT sensor dataset currently contains 50+ variables (key features shown in table 2), with more to be added from ongoing clinical record extraction. A correlation analysis of the features describing physiotherapy behaviours will remove features which are highly correlated. Variables with a Gaussian distribution will be normalised. Dimensionality reduction will be performed via principal component analysis. These methods will identify the most relevant and independent variables for cluster analysis to ensure a robust definition and visualisation of clusters.

Multiple features of ACT treatment sessions or activity days identified from the principal component and correlation analyses will be grouped using unsupervised cluster analysis, such that both the within-cluster similarity and between-cluster dissimilarity are strong. Unsupervised cluster analysis with the k-means method^18^ is a popular clustering technique and involves grouping multifactorial data into a pre-specified number of clusters. Numerous rapid computations comparing the relationship between multiple variables will determine the optimal cluster centres with the best separation between groups. The silhouette metric will be used to assess cluster homogeneity and separation, to identify the optimal number of clusters.

The associations, patterns and trends of individual physiotherapy adherence clusters to health outcomes (eg, lung function, number of hospital admissions, infections, antibiotics, etc) will be investigated with data from clinical records. Individual participant changes between clusters over time, or in relation to gaming or feedback, will also be investigated.

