### Data analysis

#### Adherence to physiotherapy

The primary outcome measures are: adherence to a participant’s daily ACT prescription (during different study phases: standard, feedback, gaming), and adherence to daily physical activity recommendations. ACT sensor (breath pressure) and Fitbit (heart rate, step count) data are processed via a data pipeline in R,^14^ within the DRE to describe these outcomes. Clinical data outcomes will be used to investigate any relationship between physiotherapy adherence and specific clinical profiles.

Adherence to medical treatment is the extent to which a patient follows the recommendations agreed upon with health professionals.^15^ As physiotherapists give personalised ACT prescriptions of varying breath count, set count and treatment session number per day, personalised adherence scores will be calculated. Daily ACT adherence will be quantified by the number and type of breaths recorded in a treatment session and per day. Cumulative, aggregate and weekly average scores will also be calculated. Adherence to the prescribed breath count (proportion of completed breaths against prescribed breaths per treatment; usually around 100 breaths), prescribed breath pressures (proportion of ideal breath pressure breaths (15–20 cmH_2_O) per treatment) and prescribed breath length (proportion of expiratory breaths at ideal length of at least 1–2 sec) and also the presence of gaps for huff and cough between sets will be assessed. A composite adherence score based on these parameters combined per session, per day and per week will be calculated.

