#### Data processing pipeline

A data processing pipeline enabling large amounts of remotely monitored sensor data to be processed efficiently, reliably and reproducibly was developed in collaboration with Microsoft computer and data science engineers. It was developed using preliminary data collected in the first 3 months of data collection (September to December 2018) and then tested on a larger dataset (to April 2019).

The pipeline ensures data are processed consistently and data validation checks at each stage alert to errors. The pipeline is being refined throughout the ongoing data collection period but, briefly, it processes data through three main steps: *data cleaning* to remove errors, *data labelling* to mark and measure predefined constructs from raw data (eg, distinct breaths from pressure traces) and finally *data featurisation*, the quantification of variables for cluster analysis. These steps and the main features for analysis are summarised in table 2.

**Table 2 T2:** Data pipeline stages and features for cluster analysis

Sensor type of data	Data pipeline step			
	Cleaning	Labelling (of)	Featurisation of variables for cluster analysis	
			Descriptive	Describing adherence*
**ACT Sensor** Pressure–Time	Removal of blank, duplicate and non-physiological values. Any non-linear baseline drift corrected, using a sparsity based de-noising approach.^19^	Treatment sessions Pressure peaks Breaths Breaks between breaths Sets of breaths	If any breaths recorded on a day Y/N Breath count† Breath length† Breath peak pressure† Treatment duration† Number of treatments per day Number of sets in a treatment† Number of breaths per set†	Adherence score (proportion of days with any breaths recorded per total number of days) Breath count adherence (proportion of completed breaths against prescribed breaths per treatment) Set adherence (proportion of sets against prescribed sets per treatment) Treatment session adherence (proportion of completed treatments against prescribed treatments) Pressure adherence (proportion of ideal expiratory pressure breaths per treatment) Breath length adherence (proportion of expiratory breaths at ideal length per treatment)

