**Fitbit** Heart rate and step count	Removal of erroneous or non-physiological data (caused by improper wearing, depleted battery, full memory capacity due to infrequent syncing). Heart rate sampling frequency made consistent (per min) using a rolling average	Gaps in data Wear time (from heart rate data) Awake wear time Time in MVPA using personalised heart rate cut-off value^17^ Points crossing MVPA cut-off value	Heart rate Resting^20^ Peak Density and variability MVPA threshold switches Step count Daily step count Density and variability Active minutes (greater than a threshold value) Combined Active minutes both heart rate and step count. Step count during periods of MVPA	Daily time in MVPA compared with 60 daily minutes recommended. Weekly time in MVPA, 7 day window compared with 420 weekly minutes recommended.

Not all features shown.

*Features quantified as adherence per prescribed treatment session, per day, per rolling 7 day week, or other time point as required for analysis. ACT prescription is taken from clinical records and physiotherapy questionnaires.

†Total and/or average per treatment, SD, min, max values.

ACT, airway clearance technique; MPVA, moderate to vigorous physical activity.

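### Scaling is stated for Gaussian variables only ahead of PCA and k-means; followed as written, this leaves the ACT adherence proportions raw and under-weighted in the clusters

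*Protocol article*

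**What the plan says.** The Statistical analysis section of the protocol article sets an order of work: highly correlated features are dropped, then "Variables with a Gaussian distribution will be normalised", then "Dimensionality reduction will be performed via principal component analysis", then the grouping step, described as "Unsupervised cluster analysis with the k-means method". The silhouette metric picks the number of clusters. No scaling is stated for a variable that is not Gaussian, and the article does not say whether PCA uses the covariance or the correlation matrix.

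On the inputs, the same section reports: "The Fitbit and ACT sensor dataset currently contains 50+ variables". Table 2 (Data processing pipeline) shows how mixed their units are. On the ACT side it lists breath count, treatment duration, peak pressure and a yes/no indicator of any breaths that day, next to six adherence features that are all proportions, the first being "Adherence score (proportion of days with any breaths recorded per total number of days". On the Fitbit side it lists "Daily step count Density and variability". The prescribed breath count per treatment is given as "usually around 100 breaths".

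**The concern.** PCA on a covariance matrix and k-means on Euclidean distance both weight a feature by its variance in the units it happens to have. Whether it is Gaussian is irrelevant to that. A yes/no variable cannot be Gaussian, and a bounded proportion is unlikely to be. The stated rule therefore passes over the features that express adherence directly and leaves them beside counts that may be hundreds or thousands of times larger.

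Clustering is the article's method for finding activity and ACT adherence profiles. The clusters are then related to lung function, admissions, infections and antibiotics, and participants' moves between clusters are followed over time and under feedback and gaming. A partition shaped by units carries into all of these.

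Raw breath count is also not a neutral stand-in for adherence. The article says that prescriptions differ between children and plans personalised scores for that reason. A cluster driven by raw breath count partly reflects how much was prescribed rather than how much of it was done.

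**Working it through.** The article gives no variance or clustering figure to reproduce, so the checks are illustrative. Every SD below is an assumption.

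**1. Weight of each feature.** Feature j has weight SD_j² / ΣSD². Thirteen Table 2 features were used. Assumed SDs (low / mid / high):
- steps 2000 / 4000 / 6000
- breath count 20 / 40 / 60
- duration in minutes 4 / 8 / 15
- MVPA minutes 15 / 30 / 45
- peak pressure 2 / 4 / 6
- breath length 0.3 / 0.6 / 1
- treatments per day 0.4 / 0.7 / 1
- four adherence proportions 0.2 / 0.3 / 0.4, and two 0.15 / 0.25 / 0.35

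The article does not say which features are Gaussian, so several readings were tried:

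| Reading | Largest weights | Six adherence proportions |
|---|---|---|
| A. Pooled, all raw | steps 99.98% | 2e-8 to 5e-8 |
| B. Pooled, only steps scaled | breath count 61-62%, MVPA 34-35% | 0.015-0.03% |
| C. Pooled; steps, breath count, duration, MVPA and pressure scaled | those five, variance 1 each | 3.8-11.2% |
| D. ACT features only, all raw | breath count 93-95%, duration 3.8-5.8% | 0.02-0.05% |
| E. Pooled, all scaled | equal | 6/13 = 46% |

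Reading D at mid values: the squared SDs of the eleven ACT features sum to 1681.3. Breath count gives 40²/1681.3 = 95.2%. The proportions give (4 × 0.3² + 2 × 0.25²)/1681.3 = 0.485/1681.3 = 0.03%. With all eleven scaled, the proportions would hold 6/11 = 55%.

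Reading C at mid values: 0.485/(5 + 0.6² + 0.7² + 0.485) = 0.485/6.335 = 7.7%.

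The result also depends on the unit chosen. With duration in seconds, its mid SD of 8 minutes becomes 480, and its weight in reading D becomes 480²/(480² + 1681.3 − 64) = 99.3%.

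**2. Recovery of true groups, ACT features only.** Setting: 145 children; two groups with mean adherence 0.4 and 0.8 (SD 0.15); breath count = adherence × prescription; prescription about 100 breaths with assumed SD 10 to 40; duration linked to breath count; k-means with k = 2. Recovery is measured by the adjusted Rand index (0 = chance, 1 = perfect).

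| | Written rule | All features scaled |
|---|---|---|
| Prescription SD 10 | about 0.6 | about 0.97-1.0 |
| Prescription SD 40 | about 0.24 | about 0.97-1.0 |

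The arithmetic explains the pattern. Group means of raw breath count are 0.4 × 100 = 40 and 0.8 × 100 = 80, a gap of 40. Within a group with mean adherence m, the variance of breath count is (m² + 0.15²) × SD_P² + 0.15² × 100², where SD_P is the prescription SD.
- SD_P = 10: m = 0.4 gives 18 + 225 = 243 (SD 15.6); m = 0.8 gives 66 + 225 = 291 (SD 17.1).
- SD_P = 40: m = 0.4 gives 292 + 225 = 517 (SD 22.7); m = 0.8 gives 1060 + 225 = 1285 (SD 35.8).

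As prescriptions vary more, the groups overlap more on breath count. Each proportion separates them by 0.4/0.15 = 2.7 SD. Six independent ones together give 2.7 × √6 = 6.5 SD, a signal that is nearly unused when the proportions hold 0.02-0.05% of the weight.

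**The case against.** The article does not say that other variables stay raw. It describes its pipeline as still being refined and shows only part of the feature list. Transforms and the choice of PCA matrix are details that a full plan may hold, so silence on them is no fault. That stands, and the point is confined to the rule the article does state, which selects variables by the wrong property. If PCA used the correlation matrix and k-means ran on its component scores, the scale problem would be largely removed. But the article says: "Multiple features of ACT treatment sessions or activity days identified from the principal component and correlation analyses will be grouped". Read plainly, the features themselves go into k-means, which does not rescale them.

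A reader might infer more: that raw step count, breath count and duration decide the clusters, and that true adherence groups are recovered no better than chance. The documents do not support that.
- Which variable dominates depends on which features are Gaussian, and the article does not say. If the large-unit ones are Gaussian, they are scaled and do not dominate (reading C).
- Step count competes with ACT proportions only if the two sensors' features are clustered together. The wording just quoted allows separate analyses. In an ACT-only analysis with duration in minutes, duration is minor.
- Chance-level recovery appears in simulation when the large-unit features are made unrelated to adherence. By Table 2's own definition, breath count adherence is breath count over prescription, so raw breath count carries signal. In the simulations above the two correlate at 0.97 down to 0.71, and the planned correlation step might drop one of them.
- Not every adherence feature is a proportion. The Fitbit ones compare MVPA time with 60 daily or 420 weekly minutes.

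The primary outcomes and the changes by study phase can also be quantified without any clusters.

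**Conclusion.** The point holds in limited form. As written, the normalisation rule ties scaling to distribution shape ahead of two scale-dependent methods. The ACT adherence proportions are under-weighted under every reading tested, from a negligible share up to 11.2%, against 46% when all thirteen features are scaled. In the ACT-only simulations the adjusted Rand index is about 0.6 to 0.24 instead of about 0.97 to 1.0: a real loss, though not a total one.

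These sizes rest on assumed SDs, on adherence groups that differ in all six proportions, on children rather than sessions or days as the clustered units, and on no scaling inside the PCA or k-means step. The consequence is confined to the cluster profiles, the moves between them and their associations with health outcomes. The directly calculated primary adherence measures are unaffected.

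**What to change.** Replace the normalisation sentence with: *Skewed features are transformed where needed, and every feature retained after the correlation step is then centred and scaled to a common (SD or robust) scale before both PCA and k-means.*

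The cost is one sentence and a few lines of R, with no new data. There is one small downside: equal weighting of the retained features is itself a weighting choice, so a behaviour described by several overlapping features counts more than once. The planned removal of highly correlated features limits this.

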**Methods and analysis:**

A cohort of 145 children and young people with CF aged 6–16 years were recruited. Each participant will record their usual physiotherapy sessions daily for 16 months, using remote monitoring sensors: (1) a bespoke ACT sensor, inserted into their usual ACT device and (2) a Fitbit Alta HR activity tracker. Real-time breath pressure during ACTs, and heart rate and daily step counts (Fitbit) are synced using specific software applications. An interrupted time-series design will facilitate evaluation of ACT interventions (feedback and ACT-driven gaming). Baseline, mid and endpoint assessments of spirometry, exercise capacity and quality of life and longitudinal clinical record data will also be collected.

This large dataset will be analysed in R using big data analytics approaches. Distinct ACT and physical activity adherence profiles will be identified, using cluster analysis to define groups of individuals based on measured characteristics and any relationships to clinical profiles assessed. Changes in adherence to physiotherapy over time or in relation to ACT interventions will be quantified and evaluated in relation to clinical outcomes.

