## Methods

### Study design

Project Fizzyo is an analytic longitudinal observational cohort study with an interrupted time-series design. Clinically prescribed ACT or exercise prescriptions for individual participants are continued as normal for the 16 months of the study. Each participant uses two remote monitoring sensors to record data daily. These are: (1) a bespoke Fizzyo ACT breath pressure sensor, inserted into their regular ACT device (Acapella Choice, Aerobika, AstraTech PEP or Pari PEP) and (2) a Fitbit Alta HR activity tracker (Fitbit, San Francisco, USA) to record daily physical activity (heart rate and step count). Participants synchronise (sync) data using software applications (apps) for each sensor, on a tablet computer provided for the study.

ACT feedback (daily number of breaths) and ACT-driven computer gaming are introduced and removed in an interrupted time series (figure 1), via the specially developed Fizzyo app. Baseline ACT patterns are recorded (during months 0–2: standard phase), then the sequential introduction of ACT feedback (during months 2–14: feedback phase) and ACT-driven gaming (during months 4–12: gaming phase) will allow any effect on breathing patterns, adherence or clinical outcomes to be observed. The removal of gaming (at month 12) and feedback (at month 14) will facilitate observation of lasting, temporary or feedback/game dependent behaviour changes.

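### Choosing the number of clusters by silhouette can never return a single cluster, so the plan cannot test whether adherence profiles are distinct, and movement between clusters has no benchmark if they are not

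*Protocol article*

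**What the plan says.** The Statistical analysis section of the protocol article reduces the features by correlation analysis and principal components, then applies k-means, a method that "involves grouping multifactorial data into a pre-specified number of clusters". The number of clusters is set thus: "The silhouette metric will be used to assess cluster homogeneity and separation, to identify the optimal number of clusters". The purpose of clustering is "to identify subgroups of participants with distinct physical activity and/or ACT adherence profiles", and the Abstract states the result as settled: "Distinct ACT and physical activity adherence profiles will be identified".

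The clusters are then related to health outcomes such as lung function and hospital admissions. The section adds: "Individual participant changes between clusters over time, or in relation to gaming or feedback, will also be investigated".

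Two other statements bear on the point. Adherence to the daily ACT prescription by study phase is a primary outcome (Adherence to physiotherapy), and before any mention of clustering the Statistical analysis section says: "Any changes in adherence to physiotherapy prescriptions or recommendations over time or in relation to ACT gaming or feedback, will be quantified".

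**The concern.** A selection rule that cannot return one cluster, paired with a promise of distinct profiles, means that the existence of profiles is assumed and not tested. If adherence varies smoothly from child to child, k-means will still cut the continuum into pieces, and the pieces will go forward as subgroups into the analyses of clinical outcomes.

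The cuts matter again when movement between clusters is examined. A child near an artificial boundary can cross it through ordinary variation from one period to the next. Under Study design, every participant goes through the same sequence of phases and no concurrent control group is described. A switch rate around the start of feedback or gaming therefore has no built-in reference for what happens when nothing changes.

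**Working it through.** The article gives no number of clusters, silhouette value, reliability or cluster separation, so there is no stated figure to reproduce. The check has four steps.

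**Inputs.** From the article: 145 participants (Abstract), k-means with silhouette-chosen k (Statistical analysis), 16 months of follow-up (Study design). Assumed: period-to-period reliability r of 0.6 to 0.95, 1 to 5 dimensions after reduction, eight two-month windows, Gaussian features, one point per child per window.

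**1. Definition.** For one point, s = (b − a) / max(a, b), where a is the mean distance to its own cluster and b is the mean distance to the nearest other cluster. With k = 1 there is no other cluster, b does not exist, and the maximum is taken over k ≥ 2 only.

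**2. What the rule returns when there are no clusters.** One Gaussian cloud, n = 145, k searched from 2 to 8, 40 runs for each of 4 dimensions and 3 reliabilities: 4 × 3 × 40 = 480 data sets. All 480 returned k ≥ 2, with choices spread from 2 to 8.

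| Dimensions | Mean winning silhouette |
|---|---|
| 1 | 0.58 |
| 2 | 0.37 |
| 3 | 0.26 |
| 5 | 0.17 |

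A separate run with k searched from 2 to 7 also never chose fewer than two and gave 0.37, 0.26 and 0.17 in 2, 3 and 5 dimensions.

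**3. Switching with no true change, no clusters present.** For one Gaussian dimension split at the mean (k = 2), two measurements with correlation r fall on opposite sides with probability arccos(r) / π.

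| r | P(switch) | Of 145 children |
|---|---|---|
| 0.6 | 29.5% | 43 |
| 0.7 | 25.3% | 37 |
| 0.8 | 20.5% | 30 |
| 0.9 | 14.4% | 21 |
| 0.95 | 10.1% | 15 |

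With silhouette-chosen k and later windows assigned to the first window's centres, the simulated ranges over 1 to 5 dimensions were:

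| r | Switch between two windows | At least one departure in 7 later windows |
|---|---|---|
| 0.6 | 48–52% | 87–91% |
| 0.8 | 28–40% | 62–76% |
| 0.9 | 18–28% | 44–62% |

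At fixed k and r = 0.8, in 2 to 5 dimensions, switching was 16–18% for k = 2, 24–28% for k = 3 and 29–35% for k = 4. The rate therefore depends strongly on how many pieces the continuum is cut into.

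**4. Contrast: two real clusters, no true change.** Two dimensions, centres a stated number of within-cluster SDs apart, 30 runs per setting. The rule chose k = 2 every time.

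| Separation | Mean silhouette | Switch between two windows |
|---|---|---|
| 3 SD | 0.47–0.48 | 7–12% |
| 4 SD | 0.57 | 2–5% |
| 5 SD | 0.64–0.65 | about 1% |
| 6 SD | 0.70 | under 0.5% |

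**The case against.** The strongest reply is that the silhouette is also meant to assess homogeneity and separation, so a low value could be reported as weak structure. That is fair as far as it goes: in two dimensions, noise scored 0.37 on average against 0.47 or more for real clusters 3 SD apart. But no cut-off is stated, and the value depends on dimension. Noise in one dimension scored 0.58, about the same as two genuine clusters 4 SD apart in two dimensions. Since the plan reduces dimensions before clustering, an uncalibrated silhouette gives little protection.

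A reader might infer that the plan counts every crossing as a behaviour change caused by gaming or feedback. It does not say so. Movement between clusters is only to be investigated, and the Study design sentence that the removal of gaming and feedback "will facilitate observation of lasting, temporary or feedback/game dependent behaviour changes" does not mention clusters. Change in adherence is also quantified separately, so the primary evidence on response does not depend on cluster labels. Stationary noise would moreover produce crossings in every phase, and is not by itself a signal of gaming or feedback.

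A reader might also infer that centres will be re-estimated in each phase, or fault the article for omitting stability checks. Neither is supported: re-clustering is not described, and a journal article may leave such detail to the full plan.

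Finally, the simulations cluster one Gaussian point per child. The article speaks of grouping sessions or days as well as individuals, and several of its features are proportions or yes/no items. The switching figures show the size of the effect under assumptions and do not forecast results for this cohort.

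**Conclusion.** The concern holds for the rule as stated. Silhouette-chosen k cannot return one cluster, so the plan has no route to the conclusion that adherence is a continuum, and the claim of distinct profiles is untested. This follows from the definition and needs no assumption.

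The concern about switching is conditional. If adherence is a continuum, no-change switching between two periods is about 20% at reliability 0.8 and 14% at 0.9 for a two-way split on one dimension, and 28–40% and 18–28% when the silhouette sets k. With true clusters 5 SD or more apart it is about 1% or less. The article gives neither reliability nor separation, so which case applies is unknown. The point should be addressed, but it does not undermine the primary adherence outcomes.

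**What to change.** - Choose k by a rule that admits k = 1, for example the gap statistic against a single-cluster reference.
- State that if one cluster is not rejected, the profiles will not be called distinct and adherence will be analysed as continuous, including in the associations with clinical outcomes.
- Report switching only against centres fixed once, for example from the standard phase, and beside the switch rate seen with no intervention change, obtained from split halves of the standard phase. That phase lasts two months, so each half is about one month; the windows compared should be of equal length, because shorter windows are noisier.
- Confirm that the response to gaming and feedback rests on change in the adherence measures already named as primary, with cluster switching as supportive.

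The cost is some wording in the analysis plan and a few lines of R. No new data are needed, and the article describes data collection as ongoing. The downside is that the study may have to report that no distinct profiles exist.
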